## Abstract

**Background:**

Sarcomas are a heterogeneous group of rare malignant tumors of mesenchymal origin in the musculoskeletal system. The main treatment is surgery often supplemented with pre-or postoperative radiotherapy.

A retrospective study by Bedi et al. indicated that negative pressure wound therapy (NPWT) reduced the risk of postoperative wound complications in patients treated with preoperative radiation followed by surgical tumor removal of lower extremity soft tissue sarcomas (STS), and the use of NPWT was not associated with an increased risk of local recurrence. Previous studies have shown that NPWT can reduce postoperative complications. STS surgeries are a high-risk procedure concerning wound complications.

**Methods:**

Non-blinded single-center randomized controlled trial comparing NPWT versus conventional wound dressing and postoperative wound complications after surgical removal of deep-seated high-malignant STS of the extremities or trunk wall

Sample-size calculation: 154 STS patients (80% risk of avoiding type II error, 5% risk of type I error, and an 80% wound complication risk)

Block randomization of 8 into:

Group A: Conventional wound dressing

Group B: NPWT (PREVENA PLUS™ Incision Management System)

Inclusion criteria: Surgery for a deep-seated STS of an extremity or the trunk wall

Exclusion criteria: Age < 18 years, plastic surgery, low malignant/borderline STS, chemotherapy, preoperative radiotherapy, allergic/hypersensitive to acrylic adhesives or silver, unwilling/unable to provide informed consent, metastatic disease, and ischemic surgeries

Primary study endpoints were set as major wound complications defined by O’Sullivan et al. as a secondary surgery under anesthesia for wound repairs and wound management without secondary surgery within 4 months postoperatively.

Secondary study endpoints among others are Musculoskeletal Tumor Society Score (MSTS), Toronto Extremity Salvage Score (TESS), and European Quality of Life - 5 Dimensions (EQ-5D).

Approval from the Scientific Ethical Committee and the Data Protection Agency has been obtained, and the study is registered at clinicaltrial.gov.

This study did not apply for external funding.

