### Statistical analysis

Fisher’s exact test will be used for categorical variables.

Depending on if the data could be considered normally distributed or not, a *t*-test for unpaired data or Mann–Whitney *U* test will be used for continuous variables.

Kaplan-Meier survival analysis will be used for overall survival (with log-rank test for comparison of groups). In case of an assumption of a difference in time to delayed wound healing, competing risk analysis will be used to address differences between the groups with death and amputation as competing factors.

All analyses will be performed in accordance with the intention-to-treat principles.

Two-sided *p*-values below 0.05 will be considered statistically significant.

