### Calculation of sample size

In the study of O’Sullivan et al. [11], a major wound complication within 4 months postoperatively was identified in 16 out of 94 (17%) STS patients treated with surgery and postoperative radiation therapy. There exist no studies evaluating the effect of NPWT on wound complications after surgery for STS combined with postoperative radiation therapy. However, in retrospective studies, it was found that NPWT reduced the risk of wound complications from 47 to 8% (83% reduction) in patients with lower extremity STS treated with preoperative radiation [14] and from 27 to 7% (75% reduction) in patients undergoing hip and knee revision surgery [20].

In a study design with an 80% risk of avoiding type II error, a 5% risk of type I error, and an 80% wound complication risk reduction in a population similar to the study by O’Sullivan et al. [11], we will need to include 154 STS patients (77 in each group) in an RCT.

To make allowance for dropouts (since the follow-up period regarding the primary study endpoint is only 4 months = 120 days few dropouts are expected) during the study period, we plan to include 160 patients.

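### The abstract misstates the effect assumption behind 154 patients as an 80% risk, and the stated 80% power is not quite reached under the planned Fisher's exact test

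*Protocol article*

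**What the plan says.** The Methods part of the abstract lists three inputs to the 154-patient calculation: 80% power, 5% type I error, "and an 80% wound complication risk".

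The section Calculation of sample size bases the same 154 (77 per group) on different content. The reference risk is a major wound complication within 4 months, which "was identified in 16 out of 94 (17%) STS patients treated with surgery and postoperative radiation therapy". The effect is "an 80% wound complication risk reduction in a population similar to the study by" that reference trial. Error rates are given as "In a study design with an 80% risk of avoiding type II error" and "a 5% risk of type I error". Enrolment is then raised to 160 to allow for dropouts.

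The section Statistical analysis states: "Fisher’s exact test will be used for categorical variables". It adds: "Two-sided *p*-values below 0.05 will be considered statistically significant". Neither section names the formula or software used to reach 154.

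**The concern.** A wound complication risk of 80% and an 80% reduction in that risk are different quantities. Taken at its word, the abstract describes an outcome that affects four in five patients and gives no effect size, so no sample size follows from it. The sample-size section describes an outcome expected in about one control patient in six, with a reduction of four fifths. Someone who sees only the abstract would have the wrong baseline risk and would not know how large an effect the trial is sized to detect. Both matter when reading a non-significant result.

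The second question is whether 80% power belongs to the test that will be used. The primary endpoint, major wound complication yes or no, is categorical and so falls under Fisher's exact test. That test is conservative when events are few, and the plan expects few: 77 × 0.17 = 13.1 in the control group and 77 × 0.034 = 2.6 in the NPWT group.

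**Working it through.** **Inputs**
- Control risk p1 = 16/94 = 0.170 (Calculation of sample size).
- Relative reduction 80%, so p2 = 0.17 × (1 − 0.80) = 0.034 (same section).
- Power 80% (same section); type I error 5%, two-sided (Statistical analysis).
- Allocation 1:1 (Study design).

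**1. Reproducing 154.** The pooled-variance normal approximation without continuity correction is

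n per group = [z(0.975) × √(2·p̄·(1−p̄)) + z(0.80) × √(p1(1−p1) + p2(1−p2))]² / (p1 − p2)²

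- p̄ = (0.17 + 0.034)/2 = 0.102
- First term: 1.960 × √(2 × 0.102 × 0.898) = 1.960 × 0.4280 = 0.8389
- Second term: 0.8416 × √(0.1411 + 0.0328) = 0.8416 × 0.4171 = 0.3510
- n = (0.8389 + 0.3510)² / 0.136² = 1.4158 / 0.0185 = 76.5, so 77 per group and 154 in total

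This matches the plan exactly. Using 16/94 instead of 0.17 also gives 77. Formula power at 77 per group is 80.2%.

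Other variants give these totals:

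| Variant | Total N |
|---|---|
| Two-sided, continuity correction | 182 |
| Two-sided, unpooled variance | 148 |
| Two-sided, arcsine | about 138 |
| One-sided, no correction | 122 |
| One-sided, continuity correction | 150 |

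Only the two-sided, pooled, uncorrected form gives 154, so it is the likely source. This is an inference.

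**2. The abstract's wording taken literally.**
- An 80% risk alone fixes no sample size.
- An 80% control risk with the 80% reduction (80% versus 16%) gives n = 8.3, so 9 per group and 18 in total.
- An 80% control risk with 77 per group has 80% power for a fall to about 59%, a relative reduction of about 26%. The article mentions no such effect.

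The 80% in the abstract therefore cannot be the event risk. It is the relative reduction stated in the sample-size section.

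**3. Power under the planned test.** For each pair of event counts (i, j) in two groups of size n, take the two-sided Fisher p-value (summing all tables no more probable than the one observed). Then add up Bin(i; n, 0.17) × Bin(j; n, 0.034) over all pairs with p < 0.05.

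| Per group | Uncorrected formula | Fisher's exact test |
|---|---|---|
| 77 | 80.2% | 76.5% |
| 80 | 81.7% | 78.7% |

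With 16/94 and one fifth of it as the two risks, the Fisher figures are 76.6% and 78.7%. Against the stated 80%, the shortfall is 80 − 76.5 = 3.5 percentage points at 77 per group and 80 − 78.7 = 1.3 points at 80 per group.

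**The case against.** The strongest reply is that one word is missing from an abstract and the same article supplies every input in full a few pages later. That is right as far as it goes. The calculation in the sample-size section is sound, no endpoint, analysis or aspect of conduct depends on the abstract, and leaving the 17% out of an abstract is ordinary condensation. What remains is that the abstract does not merely shorten the assumption; it states a different one.

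A reader might infer that the trial was sized on a wrong event rate, or that 154 is miscalculated. The documents do not support this, because the inputs in the sample-size section reproduce 154 exactly. Nor can it be said that the large assumed effect is concealed. That section states it openly, next to the retrospective reductions of 83% and 75% on which it leans.

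On Fisher's test, it is fair to say that the loss is small, that it is unrelated to the abstract's wording, and that the article never says which formula was used. All of this stands, and the Fisher point adds no weight to the wording error. A reader might infer from the continuity-corrected total of 182 that the trial is seriously too small. That figure comes from an approximation. Direct enumeration of the planned test shows a shortfall of only 1 to 4 points.

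**Conclusion.** Two limited corrections hold.

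First, the abstract misstates a planning assumption: its 80% is a relative reduction from 17% to 3.4%, not a complication risk. The error is confined to the abstract and the change in sample size is zero.

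Second, the stated 80% power is not what the planned test delivers. It is about 76.5% at the calculated 154 patients and 78.7% if all 160 are analysed. This rests on three assumptions: the planning risks of 17% and 3.4% are true, the binary primary endpoint is compared by the two-sided Fisher's exact test named for categorical variables, and 80 per group means no dropouts. That 154 came from an uncorrected normal approximation is inferred from the match; the Fisher figures do not depend on that inference.

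**What to change.** In the abstract, replace the 80% complication risk by an 80% relative reduction in wound complication risk, from 17% to 3.4%.

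In Calculation of sample size, the authors should confirm which formula gave 77 per group. They should then give the power under the planned Fisher's exact test: about 77% with 77 per group, or about 79% with 80 per group and no dropouts.

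The cost is a few words in two places and a stated power slightly below 80%. No patients are added, and the endpoint and planned test stay as they are.

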**Discussion:**

Many new medical devices and technical solutions are currently being introduced, and even though some documentation regarding the use of NPWT, e.g., in joint replacement surgery exist, it is also important to seek documentation for this treatment principle in STS surgery.

**Trial registration:**

Registered at ClinicalTrials.gov NCT04960332 and approved on 11 July 2021

## Background

Sarcomas are a heterogeneous group of rare malignant tumors of mesenchymal cell origin in the musculoskeletal system comprising 1% of all adult cancers [1]. The reported incidence of all types of sarcomas is approximately six to eight per 100,000 inhabitants corresponding to 300 cases per year in Denmark (250 Soft Tissue Sarcomas (STS) (100 retroperitoneal/abdominal STS), 50 bone sarcomas) [2, 3]. Sarcomas arise in the body’s connective tissues including bone, muscle, cartilage, fat tissue, blood vessels, and peripheral nerve sheaths and hence arise in all parts of the body, however, most dominant (78%) in the extremities [4].

There exist more than 50 histologic subtypes of STS yielding a broad heterogeneous morphology and biological behavior of all subtypes [4]. The incidence of STS increases in general with age (median age = 65) [4]. High-grade STS mostly metastasize hematogenous to the lungs, which is also the primary cause of sarcoma-specific death, and approximately 10% of patients with STS have metastases at diagnosis [5].

Treatment of STS requires a multidisciplinary highly specialized team, evaluating risks and benefits of all available options and expected outcomes with the aim to minimize the recurrence of disease and preserve function and quality of life. The main treatment principle that has largely been unchanged since the 1980s is surgery supplemented with radiotherapy depending on subtype and stage [6]. The use of negative pressure wound therapy (NPWT) after high-risk orthopedic surgeries such as amputations, treatment of open fractures, and joint replacement surgery are increasing, but the direct cost is much higher compared to the conventional wound dressing. However, previous studies have shown that NPWT can reduce postoperative complications such as wound dehiscence and infection [7–10]. STS surgery that is often combined with pre-or postoperative radiation therapy is a high-risk procedure concerning wound complications and postoperative infections [11–13]. A retrospective study showed that NPWT reduced the risk of wound complications in patients with lower extremity STS treated with preoperative radiation and the use of NPWT was not associated with an increased risk of local recurrence [14].

The purpose of this research project is to improve the surgical treatment of STS treatment based upon a randomized controlled trial (RCT). This study aims to compare standard wound closure with staples and conventional wound dressing (control group) with wound closure with staples and NPWT (interventions group). We want to evaluate the effect of the use of NPWT versus a conventional wound dressing on postoperative wound complications after surgical removal of deep-seated high-malignant STS of the extremities or trunk wall.

## Methods/design

### Study design

The study design is as follows: non-blinded single-center randomized (1:1) controlled trial, with parallel groups and block randomization of 8 patients in each group comparing NPWT versus conventional wound dressing and postoperative wound complications after surgical removal of deep-seated high-malignant STS of the extremities or trunk wall.

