### Randomization

All 160 patients will in the operating room be randomized (randomization with 80 patients in each group) to receive one of the two treatments:

Group A: Standard wound closure with staples and conventional wound dressing

Group B: Standard wound closure with staples and NPWT (PREVENA PLUS™ Incision Management System)

Block randomization with 8 patients in each block stratified for upper extremity/truncal wall or lower extremity STS will be performed using a verified computerized irreversible application—the Research Electronic Data Capture (REDCap). The randomization sequence will be computer-generated. This study is not blinded.

The study takes place at the Department of Orthopedic Surgery, Rigshospitalet, University of Copenhagen. Patients will be followed in our outpatient clinic; the surgeries will be performed by specialized orthopedic tumor surgeons. Rigshospitalet is a tertiary multidisciplinary sarcoma center performing highly specialized tumor surgeries.

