## Discussion

The surgical intervention in both groups is equal and according to current standards; the only difference is the wound dressing.

The randomization is planned as block randomization with 8 in each block; furthermore, a stratification of over extremity/trunk wall and under extremities will be performed; this is due to minimizing the risk of selection bias.

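### The block size is given in two incompatible ways, and a single fixed size published during recruitment leaves an expected 20% of allocations (11% if blocks are of 16) predictable to an observer who keeps count within a stratum

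*Protocol article*

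**What the plan says.** The protocol article describes the blocking in four places.

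- Abstract, Methods: "Block randomization of 8 into" the two groups, with no unit stated.
- Study design: a "non-blinded single-center randomized (1:1) controlled trial" with "block randomization of 8 patients in each group".
- Randomization: "Block randomization with 8 patients in each block stratified for upper extremity/truncal wall or lower extremity STS will be performed". The sequence is computer-generated and released through an irreversible REDCap application, with randomisation in the operating room. The section adds: "This study is not blinded".
- Discussion: "The randomization is planned as block randomization with 8 in each block". The sentence then adds stratification by tumour location and gives the reason: "this is due to minimizing the risk of selection bias".

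The Enrolment section places written consent on the day of surgery, after information at an outpatient visit and at least 48 hours to decide. Trial status says that recruitment had started. The article nowhere says that the block size varies.

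**The concern.** There are three linked issues.

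1. **The unit differs.** Eight per group and eight per block are different schemes at 1:1, and a reader cannot be sure from the text which one was programmed.
2. **The size is fixed and public.** Dressings are visible, one department treats every patient, and only two strata need to be followed. Once one arm's places in a block are used up, the rest of that block is known. Someone who foresees the next arm could be influenced, even unconsciously, in whom to invite or in eligibility decisions that need judgement, such as whether the wound can be closed without plastic surgery or whether the patient can comply with study procedures.
3. **The stated reason is wrong.** Blocking balances numbers, and stratification balances tumour location. Protection against selection bias comes from concealment and unpredictability, and fixed known blocks in an open trial weaken unpredictability.

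**Working it through.** **Inputs.** Allocation is 1:1 (Study design); 160 patients in two strata (Randomization); block size 8 (Randomization, Discussion) or 16 (Study design read literally, 8 + 8). The article gives no predictability figure to reproduce. Its sample size of 154 does not depend on the block scheme.

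**Consistency.** 160/8 = 20 blocks and 160/16 = 10 blocks, so the total does not settle which size was meant.

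**Certain allocations.** In a 1:1 permuted block of size 2m, an allocation is certain once one arm has received its m places. The expected number per block is 2m/(m + 1), a share of 1/(m + 1).

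For blocks of 8 (m = 4), the probability that the next allocation is certain, by position:

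| Position | Calculation | Probability |
|---|---|---|
| 1 to 4 | no arm can be full yet | 0 |
| 5 | 2/70 | 0.029 |
| 6 | 8/56 | 0.143 |
| 7 | 12/28 | 0.429 |
| 8 | 8/8 | 1.000 |

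The sum is 1.6 = 8/5, and 1.6/8 = 20.0%. Over 20 blocks, 20 × 1.6 = 32 of 160. Splitting the 160 between two strata in steps of 20, with incomplete last blocks, gives 30.4 to 32 (19% to 20%).

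For blocks of 16 (m = 8): 16/9 = 1.78 per block, and 1.78/16 = 11.1%. Over 10 blocks that is about 18 of 160.

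**Best-guess hit rate.** The observer always guesses the arm with more places left and tosses a coin when they are equal. Enumerating all equally likely blocks gives 5.33/8 = 66.6% for blocks of 8 and 10.05/16 = 62.8% for blocks of 16, against 50% by chance.

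**Alternatives.** These were simulated with two strata of 80 (an assumed split), sizes drawn with equal probability, and an observer who knows the set of possible sizes but not the order.

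| Scheme | Certain | Hit rate |
|---|---|---|
| Fixed 8 | 20% | 66.6% |
| Fixed 16 | 11% | 62.8% |
| Random 4, 8, 12 | about 3% | about 66% |
| Random 8, 12, 16 | about 2% | about 64% |

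Varying the size removes most of the certainty. It barely changes the hit rate, because arm totals still return to equality at the end of every block and a guesser can exploit that without knowing the size. The case for varying blocks therefore rests on the certain allocations.

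**The case against.** **The wording conflict is editorial.** The operative section and the Discussion agree on eight per block, the abstract is compatible with that, and only a one-sentence design summary differs. This is probably right. The line still misdescribes the allocation and needs correcting.

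**The 20% is conditional.** It applies to someone who knows the block size and tracks every earlier allocation separately in each stratum. This stands. It is an expected share available to such an observer, and nothing in the article says that anyone keeps such a count.

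**There are safeguards.** The sequence is computer-generated and released irreversibly in the operating room, after consent. These conceal the list and prevent reversal. They do not stop someone from inferring the next arm from allocations already seen, and that can happen before a patient is invited or judged eligible.

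**Stronger readings are not supported.**
- A reader might infer that the scheme produces selection bias. The document shows only an opportunity for it.
- A reader might infer that one team both takes consent and operates. The article says that the principal investigator or a colleague informs patients, and does not say who takes consent on the day.
- A reader might infer that prediction alters how the wound is closed. Both arms have the same stapled closure, and the article does not say whether randomisation precedes closure. If it does, the surgeon already knows the arm and no block size would change that.
- A reader might infer that custody of the list is deficient. An article commonly leaves that to the full protocol, so it is no finding here.

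**Conclusion.** The point holds in a limited form. The two descriptions of the block conflict, and the Study design wording is probably the one in error. With fixed blocks of 8, an expected 20% of allocations (about 32 of 160) can be known in advance; with blocks of 16, 11% (about 18 of 160). Both figures assume 1:1 permuted blocks of one fixed size and an observer who knows that size and counts within strata. Open treatment, a single centre, two strata and publication of the size during recruitment make this feasible. The consequence is avoidable exposure to selective invitation or eligibility decisions, with no evidence that it occurred. The reason given in the Discussion for blocking and stratifying is incorrect as worded.

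**What to change.** 1. Check the scheme built in REDCap and correct the Study design sentence to match it, presumably eight per block (four per arm).
2. For any allocations still to be made, use randomly varying block sizes within each stratum and do not disclose them until recruitment ends. Sizes 4, 8 and 12 bring certain allocations down to about 3% with a hit rate near 66%; sizes 8, 12 and 16 give about 2% and 64%.
3. Reword the Discussion: blocking and stratification balance group sizes and tumour location, while concealed and unpredictable allocation is what guards against selection bias.
4. If recruitment is complete, make the two text corrections, report the block scheme used and acknowledge its predictability.

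**Cost.** A new allocation list, a short amendment and a slightly larger possible imbalance at the end. An incomplete last block can leave a stratum unbalanced by at most half the block size: 4 with blocks of 8, 6 if the largest is 12, and 8 if the largest is 16. The sample size is unaffected.
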